## Abstract

**Background:**

Current management of mesenteric ischemia is primarily endovascular stent treatment. Typical CMI symptoms are postprandial abdominal pain, food fear, weight loss, and diarrhea. Revascularization is often necessary, as mesenteric ischemia may progress to bowel necrosis and death if left untreated. This study aims to compare the outcome using bare metal stent (BMS) or covered stent (CS) in the endovascular treatment of chronic and acute on chronic mesenteric ischemia.

**Methods:**

This is an investigator-driven, prospective, randomized, single-blinded, and single-center, national cohort study at the Copenhagen University Hospital, Denmark. A total of 98 patients with chronic mesenteric ischemia (CMI) and acute-on-chronic mesenteric ischemia (AoCMI) will be randomized to treatment with either BeSmooth BMS (Bentley Innomed GmbH) or BeGraft CS (Bentley Innomed GmbH). Randomization occurs intraoperatively after lesion crossing.

**Discussion:**

There is currently no published data from prospective controlled trials regarding the preferred type of stent used for the treatment of chronic and acute-on-chronic mesenteric ischemia. This trial will evaluate the short- and long-term outcome of BMS versus CS when treating CMI and AoCMI, as well as the benefit of a more intense postoperative surveillance program.

**Trial registration:**

ClinicalTrials.gov NCT05244629. Registered on February 8, 2022.

## Introduction

### Background and rationale {6a}

Chronic mesenteric ischemia (CMI) is predominantly caused by atherosclerotic [1], ostial lesions in one of the three main, mesenteric arteries: celiac trunk (CA), superior mesenteric artery (SMA), and inferior mesenteric artery (IMA). These lesions are often associated with other manifestations of atherosclerotic disease [2].

Symptomatic CMI accounts for less than 1 per 100,000 admissions; the observed rise in reported cases of symptomatic CMI aligns with the increased prevalence and precision of imaging technologies [1, 3, 4]. Atherosclerosis is the most common cause, and in most patients, the development of symptomatic CMI may take months or years to become clinically apparent. In patients with known atherosclerotic disease, the prevalence ranges from 8 to 70% and a > 50% stenosis of more than one mesenteric artery is detected in up to 15% of cases. In patients with peripheral artery disease, significant stenosis or occlusion of at least one mesenteric artery is found in 40% and 25–29%, respectively [1].

Atherosclerosis is a chronic inflammatory disease. Besides classic risk factors (cholesterol levels, smoking, high blood pressure, diabetes, and hereditary conditions), a significant coincidence between inflammatory mechanisms and symptomatic manifestation of cardiovascular disease may exist. For example, it has been shown that an increased concentration of inflammatory markers in the blood (i.e., CRP) is associated with an increased risk of atherosclerosis supporting the hypothesis that inflammatory mechanisms are essential in the development of atherosclerosis. Identification of peptides and protein from the Copenhagen Mesenteric stent study (COMESS) patients will be performed on the basis of collected data as well as in silico-generated libraries.

In this project on mesenteric ischemia, we have used a definition based on the clinical presentation: CMI, acute mesenteric ischemia (AMI), and acute on chronic mesenteric ischemia (AoCMI). CMI is defined as ischemic symptoms caused by insufficient blood supply to the gastrointestinal tract for at least 3 months. The typical presentation includes postprandial pain (88.2%), weight loss (79.2%) [5], and/or unexplained diarrhea (56%) [6]. AoCMI is defined as AMI in patients with a history of CMI. Often, the symptoms of CMI accelerate with periods of prolonged and intensified pain, pain even without eating, the onset of diarrhea, or inability to eat at all.

The abundant arterial collateral circulation of the mesenteric tract often prevents gastrointestinal ischemia in single-vessel disease. Stenosis in a single mesenteric artery is quite prevalent in the general population (up to 18%), but the diagnosis of mesenteric ischemia is uncommon partly because symptomatic CMI is rare unless two of the three mesenteric arteries are significantly stenosed or occluded [1, 7]. An exception is isolated, significant stenosis or occlusion of the SMA. This is sometimes associated with clinically relevant mesenteric ischemia as the significance of SMA flow to the intestines is particularly relevant [1].

Revascularization is indicated in patients who develop symptomatic CMI. There is no role for a conservative approach with long-term chronic parenteral nutrition and non-interventional therapy. Excessive delays in proceeding with definitive revascularization, or use of parenteral nutrition alone, have been associated with clinical deterioration, bowel infarction, and risk of sepsis from catheter-related complications [1]. The goals of mesenteric revascularization include relief of symptoms, improving quality of life, restoration of normal weight, and preventing bowel infarction [5].

Revascularization strategies to treat CMI continue to evolve with the rapid development of novel endovascular devices and techniques. During the last decade, the number of mesenteric arterial revascularizations has increased tenfold because of increasing recognition and the advent of endovascular therapy, which allows a less invasive treatment alternative. In most centers, angioplasty and stenting have become the primary treatment modalities, relegating open surgical bypass to patients who are not candidates or fail endovascular therapy [5]. The SMA is the primary target for revascularization whenever possible. Revascularization of the CA or IMA can also be performed, particularly when the SMA cannot be revascularized.

According to the guidelines from the European Society of Vascular Surgery (ESVS) as well as the US Society of Vascular Surgery (SVS), routine mesenteric stenting should be used as opposed to plain balloon angioplasty (POBA) [1, 6, 8]. In this setting, the ESVS state that CS (covered stent), as opposed to BMS (bare metal stent), may be considered, whereas the SVS recommend using CS primarily. BMS tends to form intimal hyperplasia, which is well described in the common iliac arteries, where covered stents seem to have superior patency compared to BMS. Similar tendencies are known in the setting of fenestrated aortic stent-grafting for aortic aneurysms, where CS in the renal arteries have better outcomes than BMS. The advantage of BMS is that they often require smaller access sheaths for delivery, they come on various size wire platforms, there are a large number of product types available on the market, and they are less expensive. CS sometimes require slightly larger access sheaths, are primarily delivered on a 0.035 platform, there are limited number of options commercially available, and they are more expensive.

In the current trial, CMI and AoCMI subjects will be randomized to treatment with either a BMS (BeSmooth, Bentley Innomed GmbH) or CS (BeGraft, Bentley Innomed GmbH). The metal component of the stent is identical in both groups, and the only difference is the graft covering the outside of the stent. This minimizes bias in outcomes that might be based on differing properties in the stent itself instead of the graft covering. Both the CS and the BMS are indicated and CE marked for iliac and renal stenting.

Patients with AMI will not be randomized, as this patient group is very diverse and with significant acute mortality thus preventing stable analysis of long-term stent behavior and outcome. Patients with AMI will in parallel be prospectively enrolled in a longitudinal, non-randomized cohort study according to current standard treatment.

### Objectives {7}

To assess outcomes in chronic mesenteric ischemia due to atherosclerosis, comparing the effectiveness of BMS with CS in preventing vessel re-stenosis at 12 months, and concurrently, investigate the potential advantages of an intensified postoperative surveillance program beyond current guidelines. Additionally, aim to identify inflammation-associated proteins and signaling pathways within the arteriosclerotic region of the mesenteric artery.

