### Trial design {8}

This is a single-blinded, single-center, national, prospective, randomized controlled trial comparing covered stents and bare metal stents in the treatment of mesenteric vessel stenosis in patients with CMI. The COMESS trial is a superiority trial, with two parallel groups and a primary end point of primary stent patency at 1 year. Randomization is done as block randomization with a 1:1 allocation ratio.

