### Follow-up

In this trial, patients will attend outpatient visits with clinical exams, blood samples, Duplex ultrasound (DUS), and quality of life (QoL) questionnaire at 6 weeks, 12 months, and then annually to 5 years postoperatively. CTA will be performed once at 12 months postoperatively, prior to the scheduled follow-up. In case of prohibitive traveling distance to the study site, the follow-up DUS at 1 year and beyond can be omitted from the protocol and replaced by CTA at investigators discretion. As the primary study endpoint is at 1 year, this alteration will not interfere with the conclusions. If there is suspicion of an in stent re-stenosis based on the clinical exam and DUS of the SMA (threshold 412 cm/s) [6], a patient will undergo a CTA. Following evaluation of CTA results and clinical examination, the patient may be offered additional treatment if indicated.

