### Plans to promote participant retention and complete follow-up {18b}

According to the existing standard of care (SOC), follow-up after mesenteric stenting at Rigshospitalet is an outpatient visit, including clinical examination and DUS at 6 weeks and 12 months postoperatively. According to guidelines, FU after stenting of mesenteric arteries includes clinical examination and DUS at 1 month, 6 months, 12 months, and annually thereafter [9].

In this trial, annual FU outpatient visits until the fifth postoperative year, including DUS, are planned. In addition, a CTA at 12 months has been added to validate the DUS findings. In summary, because of the present study, the participating patient will receive care in better adherence to internationally accepted guidelines using of CS instead of BMS (half of the patients) and yearly FU for 5 years instead of 1 year FU only (all patients).

If a patient chooses to not participate in the trial after randomization, patients will receive care according to current SOC.

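### The stated aim of showing a benefit from surveillance beyond guidelines has no comparator, and the protocol's own description of the guideline contradicts it

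*Protocol article*

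**What the plan says.** The Objectives section lists three aims: the stent comparison, a surveillance question and a proteomic question. The second is to "investigate the potential advantages of an intensified postoperative surveillance program beyond current guidelines". The discussion paragraph of the abstract is firmer. It says the trial will evaluate stent outcomes "as well as the benefit of a more intense postoperative surveillance program".

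Trial design {8} describes the randomised comparison: "The COMESS trial is a superiority trial, with two parallel groups and a primary end point of primary stent patency at 1 year". The two groups are covered stent and bare metal stent.

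The Follow-up section sets clinic visits with DUS and a "quality of life (QoL) questionnaire at 6 weeks, 12 months, and then annually to 5 years postoperatively", with one CTA at 12 months. For patients who live too far away, DUS from 1 year on may be omitted and replaced by CTA. Table 2 gives the modified timeline for them.

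Section {18b}, on retention and follow-up, gives two reference schedules. Local standard care has visits at 6 weeks and 12 months only. For guidelines, it says "FU after stenting of mesenteric arteries includes clinical examination and DUS at 1 month, 6 months, 12 months, and annually thereafter". It then summarises what trial patients gain over local care as "yearly FU for 5 years instead of 1 year FU only (all patients", and presents this as closer compliance with international guidelines.

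**The concern.** A benefit is a contrast: outcomes under more intense surveillance against outcomes under less. If every participant is offered the programme whatever the arm, and no outside group is named, nothing in the trial estimates that contrast.

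The reference point is also wrong. The Objectives section sets the programme above guidelines, while section {18b} describes a guideline with more first-year visits than the trial has.

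One of the three stated objectives is at stake. If the wording stays, an uncontrolled observation about surveillance could be reported as a finding of a randomised trial, with a guideline comparison that the protocol's own figures do not bear out.

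**Working it through.** **1. What the one design calculation covers.** Inputs from Sample size {14}: proportions 0.85 and 0.60, alpha 0.05 (taken as two-sided), power 0.80.

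n per group = [z(0.975)·√(2·p̄·(1−p̄)) + z(0.80)·√(p1(1−p1) + p2(1−p2))]² / (p1−p2)²

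With p̄ = 0.725:
- first term: 1.960 × √0.39875 = 1.238
- second term: 0.842 × √0.3675 = 0.510
- n = (1.238 + 0.510)² / 0.0625 ≈ 48.9, rounded up to 49 per group

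The protocol's 49 per group (98 in total) is reproduced. It powers covered against bare metal stent and nothing else.

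**2. Is there a surveillance comparator?**
- Randomised factor: stent type only (Trial design {8}).
- Schedule by arm: no difference (Follow-up; {11c}; {18b}).
- External or historical control: none named. The screening log in {20c} is kept for possible further analysis, and the AMI cohort runs in parallel. Neither is designated as a surveillance comparator.
- Planned analysis: {20a} contains no comparison of surveillance programmes, and {20b} plans no additional analyses.

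Surveillance controls: 0 of 98.

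**3. Scheduled visits with clinical examination and DUS.**

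| Schedule | Source | Year 1 | Years 2–5 | Total to year 5 |
|---|---|---|---|---|
| Guideline, as the protocol describes it | {18b} | 1, 6, 12 months = 3 | 4 | 3 + 4 = 7 |
| Trial, standard timeline | Follow-up; Table 1 | 6 weeks, 12 months = 2 | 4 | 2 + 4 = 6 |
| Local standard care | {18b} | 6 weeks, 12 months = 2 | 0 | 2 |

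The standard trial timeline has one visit fewer than the guideline in year 1 (3 − 2 = 1) and the same number in each later year. It has 6 − 2 = 4 more visits than local care, all of them after 12 months. It also adds one CTA at 12 months, which {18b} says is there to validate DUS.

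**4. The modified timeline.** Table 2 shows no physical examination or DUS after 6 weeks and a single follow-up CTA, at 12 months. Scheduled imaging after the procedure is therefore one DUS and one CTA, with telephone contact from then on.

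**5. The two statements side by side.** The Objectives section places the programme above guidelines. Section {18b} says participation moves care towards guidelines, from a local standard below them. The count in step 3 agrees with {18b}.

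**The case against.** The strongest reply is that the aim is modest. It speaks of potential advantages, investigated alongside the stent question, and Trial design {8} does not present surveillance as a randomised or confirmatory comparison. That is fair for the Objectives section. It does not cover the abstract, which says outright that the benefit will be evaluated. Even a modest investigation of advantages needs something to compare with.

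Second, visit count is a narrow measure of intensity. The trial adds a CTA, blood samples and two quality-of-life instruments to the clinical-plus-DUS schedule that the protocol quotes. This stands in part: on content the programme goes past that schedule, but on first-year frequency it does not. A reader should therefore not infer that the programme is less intense than the guideline in every respect.

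Third, a reader might infer that no endpoint touches surveillance. That goes too far. Sensitivity and specificity of CTA and ultrasound during follow-up are a secondary endpoint with a stated analysis, and restenosis, reintervention and symptom recurrence are evaluated at 5 years, well past the end of local follow-up. But test accuracy describes the tests. It does not show whether one follow-up programme leads to better outcomes than another.

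Fourth, a reader might infer that every patient has identical follow-up. The Follow-up section and Table 2 show otherwise. What holds is that the schedule does not differ by randomised arm. The reduced timeline is allocated by travel distance and the investigator's judgement, so it is no valid comparator, and it makes the word intensified harder to defend.

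Last, a fuller protocol or an SAP might name an outside comparator. Nothing shown suggests one. Neither document could turn a programme planned for both arms into a randomised contrast, and the conflict between the Objectives section and {18b} stands in the printed text.

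**Conclusion.** The point holds. The design cannot support a claim that intensified surveillance is beneficial, because it has no surveillance control (0 of 98) and no planned comparison of programmes. The guideline wording is contradicted by the protocol's own figures: 3 against 2 visits in year 1 and 7 against 6 through year 5, with one added CTA in the trial's favour. A statement that follow-up exceeds local standard care would be accurate (6 against 2 visits on the standard timeline).

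This rests on two assumptions. The guideline schedule is taken as the protocol describes it, since the guideline itself is not at hand. And no external comparator is taken to exist beyond what the article states.

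A reader might infer that the randomised stent comparison is compromised. It is not: randomisation, the primary endpoint and the sample size do not depend on the surveillance aim.

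**What to change.** In the Objectives section and the abstract, delete the benefit claim and the comparison with guidelines. State a descriptive, non-comparative aim, pooled over arms, for example:

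- **Yield of follow-up extended past local standard care:** the number and proportion of patients with restenosis or reintervention found after 12 months, with 95% CI. Say which timeline (Table 1 or Table 2) the patients followed, because Table 2 schedules no imaging after 12 months.
- **Agreement of DUS with CTA at 12 months,** in patients who had both.

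Add one sentence saying that no benefit over standard or guideline follow-up will be claimed.

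Reporting whether a restenosis was first detected at scheduled imaging or through symptoms would be informative but is optional. The article does not say that mode of detection is recorded, so this may need one added CRF item and a definition.

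The core change costs only wording and leaves a less ambitious objective. The stent comparison, the sample size of 98 and the visit schedule stay as they are.

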### Trial design {8}

This is a single-blinded, single-center, national, prospective, randomized controlled trial comparing covered stents and bare metal stents in the treatment of mesenteric vessel stenosis in patients with CMI. The COMESS trial is a superiority trial, with two parallel groups and a primary end point of primary stent patency at 1 year. Randomization is done as block randomization with a 1:1 allocation ratio.

## Methods: participants, interventions, and outcomes

### Study setting {9}

As the Copenhagen University Hospital, Denmark (Rigshospitalet) is the national referral center for patients with mesenteric ischemia, the COMESS study is a single-center trial of a national cohort. The COMESS trial is conducted at the Department of Vascular Surgery and the Department of Interventional Radiology, Copenhagen University Hospital, Denmark.

### Eligibility criteria {10}

#### Inclusion criteria

Patients with symptomatic CMI of atherosclerotic or atherothrombotic etiologyIntended endovascular treatmentSymptoms consistent with CMI (pain, weight loss, diarrhea)Significant ostial stenosis (> 50%) of the superior mesenteric artery on CTASignificant stenosis on angiography (> 50% or > 15 mmHg pressure gradient)Patients > 18 years

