### Criteria for discontinuing or modifying allocated interventions {11b}

As randomization takes place during the procedure, the patients can accept inclusion but be excluded during the proposed intervention if the identified arterial lesion is not confirmed to be significant by intraoperative pressure measurement or multiplane angiography. If a patient is excluded perioperatively, the operator will make a determination on whether the procedure continues according to standard treatment or if an alternative approach is deemed necessary.

The patient has the right to withdraw participation at any time without providing a reason. In the event of refusal or withdrawal, the patient will be transitioned to the standard care pathway for treatment.

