### Sample size {14}

In the only study investigating CS vs BMS in CMI [10], a retrospective non-randomized study of 225 patients, patients treated by CS had freedom from restenosis of 92% ± 6% compared to BMS with freedom restenosis of 53% ± 4% [10]. This study suffered several limitations that must be considered for a sample size estimation in the present RCT: the velocity cut-off used may overestimate high-grade restenosis, the follow-up was significantly longer in the BMS group, and differences in time-dependent outcomes including restenosis must be expected. In addition, a general underreporting of outcomes in both the BMS and the CS arm must be expected in a retrospective study. Therefore, the expected restenosis rates were adjusted to 85% and 60%.

Using dichotomous endpoints (restenosis: Y/N), a two independent sample study, alpha = 0.05, beta = 0.2, and power = 0.8, sample size was estimated to 49 patients in each group (total = 98). With 120 CMI/AoCMI patients treated yearly in Copenhagen, an estimated inclusion rate of 80% and 20% dropout, a total of 77 CMI patients will be randomized yearly (app 6 pts/month)—and 98 patients are expected included within 18–24 months.

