### Implementation {16c}

Eligible patients and the eventual next of kin will have oral and written information about the project by a project responsible physician or project nurse. As noted previously, randomization is done in Research Electronic Data Capture (REDCap), after the patient has provided informed consent. Randomization will be performed on an intention-to-stent basis in the angiosuite once the target lesion has been crossed with a guidewire and the lesion is determined clinically significant by angiography (> 50%) or pressure measurement (> 15 mmHg mean gradient). Only the treating team will know the allocation (CS vs BMS).

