## Statistical methods

### Statistical methods for primary and secondary outcomes {20a}

Outcomes are analyzed on intention to treat basis and secondarily per protocol. Primary outcomes will be analyzed by *t*-test and overall survival analysis, to estimate the patency at 12 months.

Secondary endpoints will be analyzed by survival analysis techniques, such as Kaplan–Meier curve and log-rank tests. ANOVA repeated measures will be used to estimate comparison QoL between the two groups, and secondary stent patency. Log-rank test will be used to compare the survival rates between groups. Sensitivity and specificity of CTA and US will be analyzed with a logistic regression and receiver operator curves (ROC) analysis.

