### Methods in analysis to handle protocol non-adherence and any statistical methods to handle missing data {20c}

Patients whom are not included in the trial for any reason are kept in a pseudonymized screening log to allow further analysis. Randomization of patients is performed on an intention to stent basis. Analysis of randomized patients will be done on an intention-to-treat analysis and per-protocol analysis will also be performed. To handle missing data, mixed models without imputation will be performed.

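### Entry requires a positive CTA and a confirmed lesion, so preoperative CTA sensitivity and specificity, and US specificity and ROC, cannot be estimated in the randomised patients against that entry definition

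*Protocol article*

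**What the plan says.** The protocol article's list of secondary endpoints ends with the sensitivity and specificity of CTA and US, both preoperatively and during follow-up. Statistical methods {20a} gives the method: "Sensitivity and specificity of CTA and US will be analyzed with a logistic regression and receiver operator curves (ROC) analysis".

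Eligibility is fixed in four places:

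- **Inclusion criteria.** An ostial SMA stenosis above 50% on CTA and a significant stenosis on angiography (above 50%, or a gradient above 15 mmHg) are listed one after the other: "of the superior mesenteric artery on CTASignificant stenosis on angiography".
- **Exclusion criteria.** A stenosis that is not significant at angiography is an exclusion.
- **Criteria for discontinuing or modifying allocated interventions {11b}.** A consented patient can "be excluded during the proposed intervention if the identified arterial lesion is not confirmed to be significant by intraoperative pressure measurement or multiplane angiography".
- **Implementation {16c}.** Randomisation takes place only once "the lesion is determined clinically significant by angiography (> 50%) or pressure measurement (> 15 mmHg mean gradient").

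Baseline duplex ultrasound (DUS) is scheduled in Tables 1 and 2, but no duplex finding is an entry criterion. The article does not name a reference standard for the accuracy endpoint. On patients who are not included, section {20c} says: "Patients whom are not included in the trial for any reason are kept in a pseudonymized screening log to allow further analysis". It does not assign them to any endpoint.

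**The concern.** Sensitivity needs reference-positive patients who could have tested negative. Specificity needs reference-negative patients. A ROC curve or a logistic model of reference status needs both classes. The entry rules select on the index test (CTA) and on the most obvious reference (angiography or pressure) together, and so appear to remove every cell of the two-by-two table except the true positives.

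At stake is the meaning of any preoperative accuracy figure the trial publishes. A CTA sensitivity of 100% would restate the inclusion criteria, yet could be read as diagnostic performance. This goes beyond detail that an analysis plan could supply: the stated endpoint and method conflict with the stated eligibility rules, and no later specification can create reference-negative patients inside the randomised set under the composite definition.

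**Working it through.** **Inputs.** 98 randomised patients (Sample size {14}); CTA above 50% required (Inclusion criteria); angiography above 50% or gradient above 15 mmHg required (Inclusion criteria, {16c}); unconfirmed lesions removed (Exclusion criteria, {11b}).

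**The plan's own figure.** The article gives no figure for the accuracy endpoint. The 98 comes from the primary endpoint and reproduces. With 85% versus 60%, two-sided alpha 0.05, power 0.8, pooled variance and no continuity correction:

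n = [1.960 × √(2 × 0.725 × 0.275) + 0.842 × √(0.85 × 0.15 + 0.60 × 0.40)]² / 0.25² = (1.238 + 0.510)² / 0.0625 ≈ 48.9, so 49 per group and 98 in total.

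This point does not touch that calculation.

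**Step 1: randomised patients, composite reference (angiography or pressure), CTA cut-off 50%.**

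| | Reference positive | Reference negative |
|---|---|---|
| CTA positive | 98 | 0 |
| CTA negative | 0 | 0 |

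- CTA sensitivity = TP/(TP + FN) = 98/(98 + 0) = 100%, whatever the true accuracy of CTA.
- CTA specificity = TN/(TN + FP) = 0/0.
- US specificity = 0/0, because there are no reference-negative patients.
- US sensitivity can be estimated, because US may be positive or negative in the 98.
- ROC curve and logistic model: a single outcome class, so neither can be fitted.

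**Step 2: add back k consented patients excluded on the table for a non-significant lesion.** They reached angiography after meeting the CTA criterion, so all are CTA-positive and reference-negative.

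- CTA sensitivity = 98/(98 + 0) = 100%, unchanged.
- CTA specificity = 0/(0 + k) = 0% for any k above zero.
- US specificity = (US-negative among k)/k, which can now be estimated, and a US ROC curve has two classes.

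**Step 3: use the pressure gradient alone as the reference.** Entry is by angiography or pressure, so some of the 98 could have entered on stenosis with a gradient of 15 mmHg or less. They would be reference-negative within the 98 and would give US some negatives. All 98 are still CTA-positive, so CTA at the 50% cut-off again has 100% sensitivity and 0% specificity. This reference would also be missing for occlusions and near-occlusions, where Intervention description {11a} omits the measurement.

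**Step 4: what the wider set can estimate.** The counts below are assumptions for illustration; the article gives none. Intervals are Wilson 95%.

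Positive predictive value (PPV) of CTA = 98/(98 + k):

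| Assumed k | PPV | 95% CI |
|---|---|---|
| 5 | 98/103 = 95.1% | 89.1 to 97.9% |
| 10 | 98/108 = 90.7% | 83.8 to 94.9% |
| 24 | 98/122 = 80.3% | 72.4 to 86.4% |

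DUS sensitivity in confirmed lesions, if 78 of 98 were positive: 79.6% (70.6 to 86.4%).

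DUS specificity, if about 80% of the k negatives were DUS-negative: 4/5 = 80% (38 to 96%), 8/10 = 80% (49 to 94%), 19/24 = 79% (60 to 91%). The quantity exists, but with few negatives it is very imprecise.

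**The case against.** The strongest reply is that the problem is narrower than a flat statement that this endpoint cannot be delivered, which a reader might infer. Much of that reply stands.

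- **The follow-up half is intact.** Entry selection does not act on restenosis status at follow-up. Section {18b} says that the 12-month CTA was added to validate the duplex findings. Only the preoperative half is affected.
- **Ultrasound is not lost altogether.** A reader might conclude that preoperative US specificity and ROC should simply be deleted. The documents do not support that. DUS is done at baseline and is not an entry criterion, so patients excluded on the table are genuine negatives for US.
- **The reference standard is not named.** A condensed article may leave it to the full protocol. A pressure-only reference could give negatives within the 98, so the 0/0 result holds for the composite reference and not for every conceivable one. A per-vessel analysis or a different stenosis cut-off could also create negatives, but the article states neither.
- **ROC analysis varies the cut-off.** Stenosis on CTA still ranges above 50%. A range-restricted CTA curve could be drawn from the wider set or against pressure alone. It would be shaped by selection and would have no patients at or below 50%.

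What does not stand is the suggestion that the screening log or another reference rescues CTA at the 50% cut-off. Steps 2 and 3 show that neither does, because nobody with CTA at or below 50% meets the trial's criteria for reaching angiography. It is fair to add that this is one secondary endpoint and that the stent comparison does not depend on it.

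**Conclusion.** The point holds in a limited form. In the 98 randomised patients, against the composite of angiography or pressure, CTA sensitivity is 100% by construction, CTA and US specificity are 0/0, and the planned preoperative logistic and ROC analyses have a one-class outcome. With the on-table exclusions added, or with a pressure-only reference, CTA at the 50% cut-off shows 100% sensitivity and 0% specificity whatever its true accuracy. US specificity and ROC can be estimated in the wider set, though only among CTA-positive patients and with few negatives.

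The conclusion assumes that the inclusion criteria apply jointly and per patient to the SMA lesion, as written. It needs no outside figure. The PPV and DUS figures rest on assumed counts and show only what could be estimated. Preoperative US sensitivity, follow-up accuracy, the primary endpoint and the sample size are not in question. The endpoint should be reworded before analysis; the trial's main conclusion is not threatened.

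**What to change.** Reword the preoperative part of the endpoint and its analysis:

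1. Define the analysis set as all consented patients who reach angiography, including those excluded during the procedure under {11b}.
2. Name the reference standard (the composite, or pressure alone). If pressure alone, say how occlusions and near-occlusions without a measurement are handled.
3. Replace CTA sensitivity and specificity at the 50% cut-off with the PPV of CTA.
4. Report DUS sensitivity in confirmed lesions.
5. Report DUS specificity and ROC only in this wider set, labelled as conditional on a positive CTA and imprecise because negatives will be few.
6. Do not report preoperative specificity or ROC from the randomised set alone against the composite reference.

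Keep the follow-up part as it is.

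The cost is wording. Baseline CTA and DUS are already scheduled, angiography and pressure measurement belong to the procedure, and the screening log already exists. The baseline DUS, CTA and angiographic results of patients excluded on the table need to be kept in analysable form. The downside is a less ambitious diagnostic endpoint.
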